**Version 1.1**

**[name] [name]**

[figure not shown]A handwritten signature in black ink, appearing to read '[name]', is centered on the page. The signature is fluid and cursive, with a long horizontal stroke extending to the right.

Principal Investigator

20    **Background**

21    Major depressive disorder (MDD) is a leading source of disability worldwide [1]. At least a  
22    third of people with MDD fail to respond to an adequate trial with first-line antidepressants  
23    and hence have varying degrees of treatment-resistant depression (TRD) [2, 3]. Treatment  
24    resistance significantly contributes to the global burden of depression [4]. Relatively few  
25    pharmacological treatments are currently available for TRD [4]. Therefore, the investigation  
26    of mechanistically novel neurotherapeutic targets (i.e. beyond standard monoamine-based  
27    approaches) for TRD is a clear unmet need in the field [4]

28

29    Statins are pleiotropic agents and accumulating evidence from preclinical studies has  
30    suggested that these agents may have antidepressant properties [4, 5]. A recent population-  
31    based study indicated that concomitant use of statins and selective serotonin reuptake  
32    inhibitors (SSRIs) resulted in significantly less psychiatric hospital contacts due to depression  
33    compared to people who used SSRIs alone [6]. Moreover, a meta-analysis of population-  
34    based studies has suggested that statin use may decrease the risk of incident depression [7]. In  
35    addition, a recent meta-analysis of three small randomised controlled studies (RCTs) have  
36    provided evidence that adjunctive treatments with statins could be efficacious for treatment of  
37    depressive symptoms in patients with moderate-to-severe depression [8].

38

39    Several mechanisms may contribute to the putative antidepressant mechanisms of statins  
40    including anti-inflammatory, anti-oxidant, neurotrophic and even monoamine-based effects.  
41    [5, 9-11] Aberrations in these pathways have been increasingly implicated in the  
42    neurobiology of depression [12-14]. Moreover, abnormalities in lipid metabolism have also

43 been implicated in the pathophysiology of depression, specifically for the development of  
44 atypical depressive symptoms i.e. increased appetite and/or weight gain, hypersomnia, leaden  
45 paralysis, fatigue and interpersonal sensitivity [15, 16]. Hence lipid-lowering effects of statins  
46 may also play a role in putative antidepressant effects of this class of drugs. Data from the  
47 STAR\*D trial indicate poorer treatment response to SSRIs in those with atypical depression  
48 and therefore, statins could provide genuinely novel therapeutic targets for this group of  
49 people with TRD [17].

50

51 We plan to carry out an RCT involving 150 participants with treatment-resistant depression,  
52 with the aim of determining whether the addition of simvastatin (20mg daily), a lipophilic  
53 statin that readily crosses the blood-brain barrier [18, 19], to treatment as usual (TAU) for 12  
54 weeks leads to a reduction in depressive symptoms compared with placebo added to TAU.  
55 We predict that treatment-resistant depression patients will show improvement in mood with  
56 simvastatin treatment and that the response will be associated with reduction in lipid  
57 biomarkers (i.e. plasma LDL and LDL/HDL ratio). A secondary hypothesis relates to  
58 simvastatin's effects on putative inflammatory biomarkers. High LDL and low HDL  
59 contribute substantially to immunological up-regulation in the development of  
60 atherosclerosis. Pro-inflammatory cytokine (Interleukin-6 and Tumour Necrosis Factor)  
61 levels are often altered in depressed patients and decreased by successful antidepressant  
62 therapy [20, 21]. We therefore predict that in those treatment-resistant depression patients  
63 who show improvement in mood with simvastatin treatment, that response will be associated  
64 with reduction in inflammatory biomarkers. Our mechanistic hypothesis is that the anti-  
65 inflammatory and lipid-reducing effects of simvastatin will improve neuroinflammation and  
66 thus mediate a response to simvastatin.

67   **Methods**

68   A pragmatic multi-centre, 12-week, double blind, placebo controlled randomised trial of  
69   simvastatin added to treatment as usual (TAU) for patients suffering from a DSM-5 major  
70   depressive episode that has failed to respond to at least two trials of antidepressants. This will  
71   be a parallel group study with 75 participants in each arm. Recruitment will occur at  
72   outpatient psychiatric clinics in Karachi, Lahore, Hyderabad, Rawalpindi and Quetta  
73   Pakistan. Consistency of procedures across sites will be ensured through vigorous training  
74   and supervision of researcher staff. This will include; ensuring research team members  
75   involved in the data collection and recording are centrally and consistently trained in the  
76   correct processes, having checklists for tasks involved in data collection, providing all  
77   researchers involved in assessments clear, written instructions through a Manual of  
78   Operations and Procedures (MOP) / Standard Operating Procedures (SOPs), which will detail  
79   operational data definitions, recruitment, screening, enrolment, randomization, follow-up  
80   procedures, data collection methods, data flow, case report forms (CRFs), and quality control  
81   procedures.

82

83   Participants will be randomised to receive either simvastatin and treatment as usual (TAU), or  
84   placebo and TAU for 12 weeks. All participants will provide written informed consent after  
85   reading the information in English and/or Urdu. Treatment as usual (TAU) will comprise of  
86   medication including antidepressants, mood stabilisers and antipsychotics and routine input  
87   from mental health services. There are little, if any provisions for psychosocial interventions  
88   to patients with depressive disorders in Pakistan. Simvastatin added to TAU will be 20mg  
89   taken once daily. This dose has been found to be safe and well tolerated as well as effective  
90   in reducing depressive symptoms in a population with moderate to severe depression [22].

91

92 The trial has been registered with Clinicaltrials.gov in (ClinicalTrials.gov identifier:  
93 NCT03435744).

94

#### 95 *Sample Size*

96 We estimate a moderate effect size of 0.60 will be reported at week 12. Assuming a type-1  
97 error of 5%, we will need to follow up 120 patients across the two groups to achieve 90%  
98 power at Week 12. With an anticipated dropout rate of 20% by Week 12, we will randomise  
99 150 participants. An effect size of 0.4 or greater for difference in MADRS scores in  
100 randomised controlled trials of antidepressants versus placebo has been suggested as  
101 necessary to suggest clinical utility for an antidepressant used as monotherapy. A sample of  
102 120 participants is therefore powered to detect moderate to large effect sizes and trends  
103 towards significance in areas of smaller effect.

104

#### 105 *Study Procedure*

##### 106 *Recruitment*

107 Initially, the research team will approach local clinical teams to inform them about the trial  
108 and provide them with the inclusion and exclusion criteria. They will then ask psychiatrists in  
109 each outpatient department if they are able to identify any patients who may be potentially  
110 eligible to take part in the study. The consultant psychiatrist will briefly explain the study to  
111 the patient and if the patient agrees, consultants will refer patients to the research team.

112

Researcher staff will work closely with the clinical team to determine if patients are suitable to participate in the trial. If patients meet the inclusion criteria, and the consultant psychiatrist and clinical team agree that they could be potential participants, the research assistant (RA) will arrange an appointment to explain the study verbally and provide them with the participant information sheet. The patient will be given at least 24 hours to read and understand this leaflet. If after this they decide that they are willing to take part, an appointment will be arranged to obtain signed informed consent for trial participation and also signed consent for access to their medical notes. Literate participants will sign the consent forms but, if the participant cannot read and sign the consent form, his/her caregiver and/or an independent person who the participant agrees to be a witness, will be requested to read the participant information leaflet and consent form to patient. Participants will then be asked to place a thumbprint on the consent form if they agree to participate, which will be countersigned by a witness/caregiver.

### *Screening*

At the first visit, participants will undergo structured diagnostic interviews using the Structured Clinical Interview for DSM-5 (SCID-5) to confirm a diagnosis of DSM-5 current major depressive episode [23]. This tool has been validated for use in the Urdu language and has been used in previous studies in Pakistan [24]. The 24-item Hamilton Rating Scale for Depression (HRSD-24) will be used to assess severity and a score  $\geq 14$  will be used as the minimum threshold for study entry [25].

All patients must currently be on an antidepressant and must have had a non-response to  $\geq 2$  oral antidepressant treatments in the current episode (including the one they are currently

taking). The  $\geq 2$  antidepressants must have been taken for at least 6 weeks at least at the minimum therapeutic dose according to British National Formulary (BNF) [26] and Maudsley prescribing guidelines [27]. Relapse whilst on an antidepressant will also count as a failed treatment trial. During the twelve weeks of active/placebo treatment patients will be requested to remain on a stable dose of the antidepressant they are taking. Participants will not be permitted to start a psychosocial intervention or psychotherapy during the study period, however those who were already engaged in these treatments at the screening stage will be permitted to continue their treatment.

#### *Inclusion Criteria*

Male and female patients aged 18 to 75 years; diagnosis of major depressive episode confirmed by SCID-5; two or more failed trials of antidepressant medication, at minimum effective doses (as per BNF and Maudsley Prescribing guidelines) for at least 6 weeks; in contact with mental health services; able to demonstrate the capacity to provide informed consent as assessed by their own clinician; able to complete the required evaluations and take oral medication; effective contraceptive precautions (either the use of barrier methods or the oral contraceptive pill) to be taken by women of child-bearing age.; a negative pregnancy test will be required in order to meet inclusion criteria.

#### *Exclusion Criteria*

Primary psychotic disorder or bipolar disorder; history of intolerance to statins or presence of any contraindication to statins; presence of any serious medical condition or neurological problem; presence of autoimmune or inflammatory disorder (e.g. systemic lupus

erythematous, rheumatoid arthritis and inflammatory bowel disease); alcohol or drug dependence; active suicidal ideation; pregnant or breast-feeding. Patients with a serum low density lipoprotein (LDL) level of <80 mg/dL at baseline are also excluded from the study as are patients with abnormal hepatic enzymes (Aspartate transaminase (AST) and Alanine transaminase (ALT)) or abnormal Lactate Dehydrogenase (LDH) or Creatinine Phosphokinase (CPK) values at baseline. Patients already on statin treatment will also be excluded.

The criteria for leaving the study are: (1) at the participant's request; (2) at the discretion of the responsible physician or trial investigator (e.g. an adverse event, poor compliance). Poor compliance is defined as either taking <75% of study medication between assessments points at baseline, week 2, 4, 8 and 12 or missing trial medications all together for  $\geq 7$  days in period (3) pregnancy.

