#### *Randomisation and Allocation Concealment*

Randomisation service will be provided by an independent statistical support service based in the UK. We will stratify randomization based on severity of depressive symptoms at baseline and study centre. Participants will be assigned to groups via random generation of allocation sequence, balanced across allocation group. Each participant will be assigned a unique study patient identification number once they have given informed consent and eligibility has been confirmed. The central trial pharmacist will prepare a 12-week package of treatment bearing the patient's name and ID number and send it to the site pharmacy. Thus, the site pharmacy will not know the treatment allocated to the patient. A study information leaflet will be given

to the participant, explaining that they are in a clinical trial and that in addition to TAU they are taking a placebo or simvastatin. This leaflet will also have the name of the local PI's.

Allocation will be masked from study investigators and co-investigators until participants have completed all follow-ups and the database is cleaned and locked. The trial pharmacist at the central pharmacy will keep the drug codes. There will be detailed protocols regarding maintenance of blindness for raters and governing unblinding procedures in case of emergency for pharmacists. To assess the integrity of blinding procedures, participants and independent raters will be asked to complete a conventional guess form asking whether they believe participants received simvastatin or placebo as a treatment after the final ratings have been completed.

If any participant develops side effects or suffers an emergency requiring drug unblinding, the responsible consultant and care team will be informed of the trial drug, probable side-effects and make a decision of participant continuation in the trial. Participant well being and safety will be crucial at all times and locally and internationally accepted Good Clinical Practice will be observed across the trial's governance procedures

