#### *Statistical Analysis*

Initial descriptive analysis will be conducted to study the profile of the subjects and investigate group differences at baseline on main demographics and clinical measures. Frequencies and proportions will be used for categorical variables and mean and standard deviations, median and inter-quartile range, minimum and maximum for continuous variables. No statistical significance tests will be used to compare groups. Drop out, visit frequency and adherence to treatment will be summarized by group with the appropriate descriptive statistics.

The main analysis will follow the Intention-to-treat (ITT) principle in which subjects are assigned to treatment groups as randomized. Subjects that drop out of the study will be included in the analysis provided that they have a baseline score for the outcome. For the primary hypothesis, the MADRS scores at week 12 will be compared between groups using a mixed effect model. The outcome for the model will be all post-baseline MADRS scores and the fixed effects will include baseline MADRS scores, treatment group, time (post-baseline timepoints) and a treatment group by timepoint interaction. To account for the dependencies between repeated measures on the same patients, an intercept for each individual will be included as a random effect. A linear contrast will be used to test the primary hypothesis, the difference between groups in at week 12 in MADRS scores. Given the modest sample size it will likely not be possible to use as random slope for each subject, however the covariance matrix of the residuals of the model can be allowed to correlate to account for dependencies across time. Two tailed tests and an alpha level of 0.05 will be used for significance. All estimates will be presented with the 95% confidence interval. To give an estimate of effect size, standardized regression coefficients will be calculated using the overall SD of the baseline outcome scores as the metric. One advantage of this approach is it gives the magnitude and direction of effect in units of patient population of interest.

275

276 Secondary analyses will use similar mixed models to that of the primary outcome, baseline  
277 adjusted with time, treatment group and the interaction between treatment group and time as  
278 independent variables. As for the primary outcome, the main timepoint of interest is 12 week  
279 follow up and treatment effects will be determined by contrasts at the measured timepoint.  

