280 To compare response and remission rates between groups logistic regression will be used in  
281 which patients will be classified as in remission or not according to standard criteria on the  
282 MADRS scale. As there are multiple measures, p values will be adjusted for multiple  
283 comparisons using a correction based on controlling the family-wise error. Outcomes at  
284 timepoints other than 12 week follow-up will be considered exploratory and the main focus  
285 will be effect sizes (standardized regression coefficients).

286

287 To compare frequency of adverse events descriptive summaries will be presented by  
288 treatment group. Differences in the rates of AEs will be assessed by generalized linear mixed  
289 model with Poission or negative binomial distribution will be used given sufficient numbers  
290 of events, where time, treatment group and their interaction are fixed effects with subjects as  
291 random effects. Alternatively, simple count models will be used at each timepoint given the  
292 limited sample size and complexity of GLMM models.

293

294 It is likely there will be some drop-out of participants from the trial. Baseline predictors of  
295 missingness can be identified using logistic regression with the outcome (missing or not).  
296 Mixed effect models fitted through maximum likelihood can use all available information in  
297 the data potentially avoiding removal of dropout subjects from the analysis. Moreover, by  
298 including baseline predictors of missingness in the statistical models, the analysis may

assume the data to be missing at random (MAR). Diagnostic analysis will be conducted through checking residuals for outliers, influential data points and normality. If outliers or influential points are found a sensitivity analysis will be conducted after removing such points to see if the main findings change.

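### Adverse events and poor compliance can end a participant's time in the study, not only their trial medication, so week-12 MADRS scores may be lost and the intention-to-treat comparison may not be fully delivered

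*Protocol*

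**What the plan says.** The Exclusion Criteria section of the protocol ends with a list that opens "The criteria for leaving the study are: (1) at the participant's request". The second item allows removal "at the discretion of the responsible physician or trial investigator (e.g. an adverse event, poor compliance". The third is pregnancy. The same paragraph gives poor compliance a numerical meaning: "Poor compliance is defined as either taking <75% of study medication between assessments points at baseline, week 2, 4, 8 and 12", or missing the trial medication entirely for at least 7 days.

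Randomisation and Allocation Concealment adds a second route. When side effects or an emergency require unblinding, the consultant and care team are told the allocation and then "make a decision of participant continuation in the trial".

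The Methods section describes the trial as pragmatic. On analysis, Statistical Analysis says: "The main analysis will follow the Intention-to-treat (ITT) principle in which subjects are assigned to treatment groups as randomized". It continues: "Subjects that drop out of the study will be included in the analysis provided that they have a baseline score for the outcome". The primary model is a mixed model for which "The outcome for the model will be all post-baseline MADRS scores". On missing data, the section notes that maximum likelihood uses all available data. It then says that, by "including baseline predictors of missingness in the statistical models, the analysis may" treat the data as missing at random.

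**The concern.** The listed criteria govern leaving the study, not stopping tablets. The protocol never distinguishes the two, and it schedules no MADRS for someone who has left. A participant removed after week 2, 4 or 8 would then have no week-12 score, which is the primary outcome. Someone removed before any follow-up rating would add no outcome data at all, although the text counts them as included because they have a baseline score.

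The reasons for these losses arise after randomisation and may differ between arms. In the unblinding route, the decision is taken by people who know the allocation. An intention-to-treat comparison asks what happens to everyone assigned to simvastatin, including those who take it poorly or stop. If their later scores are never taken, the model has to extrapolate them from scores collected while participants were still in the study. The estimate may then move away from the effect of assignment and towards the effect under continued participation. An analysis plan can examine sensitivity to this, but it cannot recover ratings that were not made.

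**Working it through.** **1. The plan's own figures.** Inputs from Sample Size and Statistical Analysis: effect size 0.60, two-sided alpha 0.05, power 90%, 20% dropout.

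- Normal approximation per arm: 2 × (1.960 + 1.282)² / 0.60² = 58.4, so 59 per arm (118 in total). The t-test version gives 59.35, so 60 per arm, which is the plan's 120.
- Dropout: 120 / (1 − 0.20) = 150, as stated.
- Power with 60 per arm (t-test): 90.3%.

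The sample size is sound. The 20% allowance restores numbers; it does not restore the scores of those who leave.

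**2. When scores can be lost.** Follow-up places the pill count at each follow-up visit, and Table 1 schedules MADRS at the same visits.

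| Poor compliance found at | MADRS at that visit | Later MADRS at risk if removed |
|---|---|---|
| Week 2 | available | weeks 4, 8, 12 |
| Week 4 | available | weeks 8, 12 |
| Week 8 | available | week 12 |
| Week 12 | available | none |

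Removal for an adverse event can happen at any time, including before week 2.

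**3. Size under stated assumptions.** The documents do not say how many would leave for these reasons or how they would fare, so both are assumed here. Let p be the share of the simvastatin arm that leaves and r the fraction of benefit still present in them at week 12. Take the effect in those who stay as the plan's 0.60.

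- As-randomised effect = 0.60 × [1 − p(1 − r)]
- Overstatement if the model reports 0.60 = 1 / [1 − p(1 − r)] − 1

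| p | r | As-randomised effect | Overstatement | Power, all 75 per arm followed |
|---|---|---|---|---|
| 10% | 0.5 | 0.570 | 5% | 93% |
| 15% | 0.5 | 0.555 | 8% | 92% |
| 20% | 0.5 | 0.540 | 11% | 91% |
| 10% | 0 | 0.540 | 11% | 91% |
| 15% | 0 | 0.510 | 18% | 87% |
| 20% | 0 | 0.480 | 25% | 83% |

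**4. Do the earlier scores repair this?** One large data set per share (4,000 per arm) was simulated and analysed with a random-intercept mixed model as in the protocol. Assumptions: within-person correlation 0.5; effects 0.15, 0.30, 0.45 and 0.60 at weeks 2, 4, 8 and 12; the same share leaving each arm at random after week 4; no benefit once off simvastatin.

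| Share leaving | Week-12 effect, scores end at leaving | Week-12 effect, all followed | Difference (SD) |
|---|---|---|---|
| 5% | 0.60 | 0.57 | 0.03 |
| 10% | 0.62 | 0.55 | 0.07 |
| 20% | 0.57 | 0.46 | 0.12 |

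Keeping the scores from before departure did not close the gap in this setting. The simulation assumes r = 0, so it corresponds to the lower half of the table in step 3. Leaving was unrelated to mood and equal in both arms, so any further selection effect, in either direction, is not included.

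**The case against.** The case on the other side has five parts.

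- **Leaving is discretionary, and the text does not say that ratings cease.** Both points are correct. A reader might infer that outcome data certainly stop and that intention-to-treat is simply not delivered. The documents do not support this: the end of assessment follows only from the words about leaving the study and from the absence of any later follow-up, and very few might be removed.
- **Intention-to-treat as the protocol words it is respected.** Participants are analysed in their assigned arm and dropouts are not deleted. This stands as far as it goes, but an analysis set does not supply week-12 scores that were not collected.
- **Missing at random does not rest on baseline alone.** A reader might take the remark on baseline predictors that way. However, the likelihood-based model also conditions on each leaver's observed MADRS scores, so poor tolerability or adherence that already shows in mood is partly captured. Nor are leavers simply treated like good compliers, since poor compliers may remain. The bias is reduced, but adherence and adverse events themselves are not in the model.
- **The large figures are a worst case.** This is correct. The 25% needs all of the 20% dropout to have these causes and no benefit to be retained, although participant request and pregnancy are also listed and someone taking just under 75% of tablets counts as a poor complier.
- **The estimand and sensitivity analyses may be in an SAP that is not shown.** That may be so, and their absence is not criticised here. Whether ratings continue after medication stops is a matter for the protocol.

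**Conclusion.** The point holds in moderated form. By making adverse events and poor compliance grounds for leaving the study, and by letting a care team that knows the allocation decide on continuation, the protocol permits MADRS scores up to week 12 to be lost for post-randomisation reasons. The intention-to-treat comparison may then be incomplete.

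The size cannot be determined from the documents. With 10% to 20% of the simvastatin arm leaving for these reasons, the as-randomised effect would be overstated by about 5% to 11% if half the benefit is retained and 11% to 25% if none is. These shares and retention fractions are assumptions. Poor compliance found only at the week-12 visit need lose no primary data. The sample size calculation is not in question.

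This should be fixed before the primary analysis depends on it, but the evidence does not make it a fatal defect.

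**What to change.** Leave the criteria for stopping trial medication as they are; no view is taken here on when medication should stop. In the protocol:

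- State that anyone who stops trial medication or takes it poorly remains in the study and is assessed at all remaining scheduled visits to week 12, unless they withdraw consent to follow-up.
- State that these scores enter the primary mixed model in the randomised arm.
- Record adherence, and the date of and reason for stopping medication, as data and not as grounds for ending follow-up.
- Reconcile the leaving criteria in Exclusion Criteria and the continuation decision in Randomisation and Allocation Concealment with the intention-to-treat statement in Statistical Analysis.

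The cost is a wording change plus visits already in Table 1 for people who would otherwise have left. The estimated effect may be smaller because it includes non-adherers. Under the assumptions above, power with all 75 per arm followed is 91% to 93% with half the benefit retained and 83% to 91% with none, for shares of 20% down to 10%.
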